# LIST OF ACRONYMS

ANC Antenatal Care

HIV Human Immunodeficiency Virus

HTC HIV testing and counseling

IDI In-depth Interview

IPV Intimate Partner Violence

IRDO Impact Research & Development Organization

KEMRI Kenya Medical Research Institute

LHC Lumumba Health Centre

ODK Open Data Kit

PPC Postpartum Care

RA Research Assistant

SOP Standard Operating Procedures

UNC-CH University of North Carolina at Chapel Hill

VCT Voluntary Testing & Counseling

|  |  |
| --- | --- |

# INTRODUCTION/BACKGROUND

Increasing the uptake of HIV testing and counseling (HTC) in sub-Saharan Africa is essential for improving the effectiveness of HIV treatment and preventing new HIV infections. Although Kenya has nearly met its target of 80% coverage of HTC among adults, uptake of HTC among men, uptake of repeat testing, and knowledge of HIV status among HIV-infected persons remains low[1, 2]. Whereas early diagnosis and treatment reduces transmission[3-5], improves survival and reduces long-term morbidity[4, 6, 7], late diagnosis is more common and a major contributor to high rates of early mortality in African HIV care programs[8, 9]. Low HTC uptake therefore limits the impact of combination HIV prevention, including treatment as prevention strategies.Existing efforts to encourage women to refer their male partners for HTC and thereby address the male testing gap have had limited success. Moreover, despite the benefits of couples testing – greater likelihood of mutual HIV status disclosure and adoption of antiretroviral therapy for HIV prevention – the majority of HIV testing takes place alone and not with sexual partners. Innovative use of HIV self-tests provides an opportunity to address the challenges of low uptake of HIV testing among men and among couples.

Since adult men are significantly less likely to seek HTC than women, finding novel ways to close the male testing gap is a major priority. Women in Kenya access HIV testing at higher rates than men, in large part due to the offer of routine HIV testing for pregnant women at antenatal clinics and generally higher healthcare utilization among women. Results from the Kenya AIDS Indicator Survey (KAIS) indicate that only 62.5% have ever tested for HIV and of those, only 63.9% had tested for HIV more than once (compared to 80.4% and 73.3% of women)[10]. These data along with other studies have pointed to the need for innovative HIV testing strategies for men [10]. One commonly used method for engaging more men in HTC has been to recommend to pregnant women that they ask their partners to accompany them for antenatal care [11]. But in practice this approach has not succeeded in increasing uptake of HTC by men in a significant manner. The proportion of Kenyan men accompanying female partners to antenatal appointments is low (16%) although encouragingly 95% of those accept HIV testing [12].

Couples testing also has important HIV prevention benefits and has been recommended for scale-up, but there has been limited success in increasing its uptake.Couples testing has been recommended by the World Health Organization’s guidelines along with support for mutual disclosure of HIV status and antiretroviral therapy (ART) for serodiscordant couples[11]. Foremost among these benefits is the possibility of better sexual decision-making (for example, marital and fertility decisions). Individuals in couples who test together and mutually disclose their HIV status are also more likely than those testing alone to adopt a range of HIV prevention behaviors. Among HIV-infected pregnant women in particular, couples testing can results in greater support for uptake and adherence to prevention of mother-to-child transmission (PMTCT) interventions. Among serodiscordant couples, the benefits include a greater likelihood of ART uptake and adherence to improve the HIV-infected person’s health and reduce HIV transmission risk; as well as the possibility (in some cases) of the uninfected individual accessing pre-exposure prophylaxis (PrEP) to prevent HIV acquisition. Despite these benefits,according to the KAIS data only 37.2% of testers had reported ever testing together with a sexual partner [10].

Low uptake of HIV testing among men and among couples in Kenya is concerning in light of data indicating that 4 in 10 new HIV infections occur within stable heterosexual partnerships and the majority of persons in serodiscordant relationships are unaware of their HIV status [13].Although HTC is available free-of-charge in most places, for many individuals and couples the barriers to testing include stigma, fear of prognosis, lack of awareness of HIV risk, inconvenience, fear of disclosure, transportation costs, opportunity costs such as time off from work, and behavioral factors such as a tendency to put off behaviors with immediate costs and delayed benefits [14, 15].

Oral fluid-based HIV self-testing is a promising biomedical technology that has the potential to overcome many barriers to HIV testing.Self-tests, which enable individuals to test themselves and their partners for HIV privately, may first and foremost help to increase the number of people who are aware of their own HIV status. Self-tests also provide individuals with an opportunity to initiate testing with their sexual partners, a possibility that could have significant implications for HIV prevention.With self-testing, individuals collect their own sample and perform a simple, rapid HIV antibody test in the absence of a provider. It offers increased convenience, privacy, and autonomy, and has the potential to increase normalization of regular testing. With the development of simple, oral fluid-based tests, regulated self-testing has recently been adopted in Kenya [16].

Existing research shows a high level of acceptability and demand for self-testing. Importantly for our intervention, men in Kenya have shown considerable openness to self-testing [10, 17]. In studies from the US, Europe and Africa, 73% to 89% of people have reported interest in, preference for, or belief that self-testing should be made available[18-24]. Interest is typically highest among high-risk groups and those who have never tested for HIV [20-22]. In a community-based study in Malawi, 92% of participants opted for supervised self-testing over provider-delivered HTC, including a high proportion of first-time testers[25]. Data from six European countries indicated that 67% of self-testers would not have tested through provider-delivered HTC [26].These data suggest that HIV self-testing has the potential to reach new populations who are not comfortable accessing existing HTC services. Respondents from a range of studies report that self-testing would reduce or eliminate stigma around HIV testing, a formidable barrier, as well as increase convenience and confidentiality [18, 21, 22, 27, 28]. In terms of accuracy of self-testing, US emergency room patients achieved 100% accuracy, and in the study in Malawi accuracy was >99% [25]. The FDA-approved Oraquick In-home HIV test achieved 92% sensitivity in premarket self-testing in the US [29]. A recent study in Kenya found 92.9% sensitivity and 97.8% specificity [30].

A promising but under-explored use of self-testing is the provision of multiple self-tests to individuals who are then encouraged to distribute the self-tests in their sexual networks.Given the low uptake of HTC by men and by couples so far and the high risk of HIV infection among individuals in stable heterosexual partnerships, an especially promising use of self-testing could lie in the initiation of partner testing or couples testing by providing multiple self-tests to index individuals who are in stable partnerships [31]. So far there is limited evidence on the feasibility of a strategy that would provide multiple HIV self-tests to an individual and encourage them to use the tests to make more informed sexual decisions and better protect themselves from acquiring HIV. A small qualitative study in Malawi found that couples were able to use self-testing to facilitate mutual HIV-status disclosure, which further supports the feasibility of our intervention [32]. While such use of self-tests within partnerships in sub-Saharan Africa is highly innovative, there have been efforts to use self-tests in this way in pilot studies among men who have sex with men (MSM) in New York City [21, 33, 34]. MSM were able to use self-tests to screen potential sexual partners for HIV and decide whether to use condoms or avoid sex altogether when partners declined to test or when an HIV-positive result was obtained. Learning whether such an approach would work among couples in high HIV prevalence settings is vital for determining the full potential of self-testing as an HIV prevention.

Our intervention will consist of providing pregnant and post-partum women with multiple HIV self-tests so that they can then provide the tests to people who currently have lower uptake of HTC – their male partners. In this way, our intervention seeks to increase uptake of HIV testing among men.

# JUSTIFICATION

The proposed intervention helps overcome many of the barriers to uptake of facility-based HTC among men such as reluctance to visit healthcare facilities, stigma, and costs such as transportation and lost wages. The intervention leverages the advantages of self-tests – greater privacy and ease of use – while also using the female partners of men to advocate for HIV testing rather than other ways to promote testing among men that may be less effective. In the proposed intervention, women will be given two HIV self-tests and encouraged to either provide one self-test to their male partner for own use (partner testing) or to use the two tests together with their partners (couples testing). Since self-tests have advantages over facility-based HTC, the pilot intervention we will implement has the potential to achieve higher uptake of HIV testing among male partners than the current standard of care that encourages pregnant and post-partum women to refer their partners for HTC at fixed sites. The impact evaluation of the pilot intervention will use a randomized trial design to assess the effect of the intervention relative to the standard of care. Outcomes studied will include uptake of HIV testing among male partners, uptake of couples testing, reported adverse events, and linkage to care.

Our rationale for providing multiple self-tests to pregnant and postpartum women attending antenatal and postpartum clinics also lies in the special importance of partner or couples testing taking place in this population.Women have ongoing risk of acquiring HIV in pregnancy and postpartum [35]. Due to elevated risks of HIV transmission (female-to-male) and acquisition (male-to-female) during pregnancy – as well as the greater risk of maternal-to-child transmission if women have higher viral loads as a result of becoming newly infected during pregnancy or postpartum – it is particularly important that partners of pregnant women receive HTC. In fact, partner and couples HTC has been strongly endorsed by the WHO and fairly widely promoted in antenatal care settings [11]. The key challenge however, has been in promoting widespread *uptake* of either partner or couples testing in ANC settings. In most countries including Kenya only a small proportion of male partners attend ANC or postpartum clinics (PPC) with their partners and get tested with them [12, 36].

Novel data are also needed to determine whether the provision of multiple self-tests to women for the purpose of promoting partner or couples testing can be done without increasing the risk of intimate partner violence (IPV).One concern with the promotion of couples HTC in ANC settings has been IPV if one or both partners test HIV-positive. Results to date have been mixed; one randomized controlled trial (RCT) showed no effect of couples HTC on IPV whereas two observational studies found that women who received couples HTC reported more physical violence (3.3%) than women who receiving individual HTC (1.1%)[37-39]. It is important to establish whether IPV is any more likely to occur when women provide their partners with a self-test for individual use or when they initiate couples testing using self-tests. By virtue of being the first attempt to promote partner or couples testing using self-tests, our intervention and accompanying evaluation will provide much-needed evidence to determine whether such testing should be a paradigm that is adopted more widely.

Our intervention builds upon existing work that we have done to explore the acceptability and feasibility of an approach to provide self-tests to index persons for the purpose of promoting more widespread HIV testing in their sexual networks.With support from the Bill and Melinda Gates Foundation’s Grand Challenges Explorations program, our team has begun implementing a pilot intervention to explore the acceptability and willingness among women in Kisumu to use self-tests with their sexual partners. The early findings from our research will be essential for developing counseling protocols that accompany the intervention and developing strategies that facilitate the ability of women to bring up the issue of self-test usage with their partners.

# STUDY OBJECTIVES AND HYPOTHESES

This study will use a randomized controlled trial design withindividual-level random assignment to test whether offering multiple self-tests to women can increase the likelihood that either partner or couples testing takes pace. Our hypothesis is that the intervention group will have higher uptake of HIV testing by women’s partners within 3 months of enrollment in the study than the control group.

### Primary Outcome Measures

The primary outcome for the study will be uptake of HIV testing by women’s partnerswithin 3 months of enrollment in the study. For each participant, we will record whether the participant’s partner underwent HIV testing – in the case of the intervention group, this will be a report by female study participants that their partner used a self-test; in the control group, this will be uptake of HTC at the VCT by the partner. We will test for differences in the primary outcome variable between the intervention and control group.

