**Recording uptake of voluntary HTC (control group)**

At the time of enrollment participants in the control group will be provided with referral vouchers (with a unique participant ID code) for HTC (at LHC or another facility of their choice within and around Kisumu) that they and their partners can use for either partner testing (partner tests alone) or couples testing. In the 3 months after enrollment, we will be able to clearly determine whether participants’ partners came for HTC either individually or as a couple based on whether the referral vouchers were presented at HTC sites.

Research assistants at LHC, KEDH and Rabuor Health Centrewill collect and record the referral voucher numbers (with a unique participant ID code) presented at the HTC sites when an individual comes for HIV testing. They will record whether participants’ partners presented these vouchers in the 3 months after enrollment in order to obtain information on utilization of testing by both intervention and control groups. This strategy has been successfully implemented in previous studies that our team has conducted in the Nyanza region of Kenya, including impact evaluations supported by the Gates Foundation and 3ie in which we record uptake based on presentation of referral vouchers.

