# STATISTICAL CONSIDERATIONS

## Statistical analysis

Our primary analysis will use logistic regression to report unadjusted and adjusted odds ratios for the effect of the intervention on uptake of HIV testing by the primary partners of study participants. The primary outcome variable (defined in detail above) will be a binary variable indicating whether or not the partner of each participant was reported to have tested for HIV (either with a self-test in the case of the intervention group or at a VCT in the case of the control group). Logistic regression models will be estimated in STATA with and without controls for age, education, indicator of whether the participant is seeking antenatal or postpartum care, and partner characteristics (age, education, employment status). All other statistical tests that compare the intervention and control groups will be 2-sided and significance will be set at P < 0.05.

In secondary analyses, we will also estimate logistic regression models in which the effect of the intervention on secondary outcomes defined above is studied. For example, we will examine whether HIV testing was more likely to be suggested to primary partners in the intervention or control groups. Similarly, we will assess the effect of the intervention on other secondary outcomes including mutual disclosure of HIV status and incidence of adverse events.

Finally, to assess the potential for using self-testing to promote HIV testing among male partners of HIV-infected and HIV-uninfected women, we will also carry out analyses in which we compare whether the uptake of HIV testing by participants’ partners and mutual disclosure differs between HIV-infected and HIV-uninfected women.

We will conduct sensitivity analysis using inverse probability weighting to correct for selective uptake of the intervention. This robustness test predicts the probability of intervention uptake using the baseline variables and reweights the estimates to make them more representative.

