# LIMITATIONS

This study has several limitations that warrant discussion. We recognize the limitations of relying on self-reported HIV testing as an outcome variable. This is an inherent issue in all studies to date that have measured the use of self-tests, since the self-tests are typically used in private. We will take several steps to overcome the limitations of having self-reported outcomes in the intervention group and an objective outcome in the control group. First, in the intervention group, during the follow-up interview we will ask to see the used self-testing package in cases where study participants report that they or their male partner used the self-test (this has previously been done in other studies in Malawi). While the verification of used self-testing packages is not necessarily a flawless measure of actual usage of self-testing, it will provide some indication of how much higher the self-reported measure is relative to the verified measure. Second, we will also explore ways to verify whether the participants’ partner sought confirmatory testing after using the self-test: If the participant states that their partner went for a confirmatory test, we will check whether the referral voucher given to them were recorded at the VCT that they visited.

In comparing the intervention and control groups, we will also examine a self-reported outcome that will be similar in both study arms so as the reduce bias in the estimated effect of the intervention: in particular, we will ask study participants in both groups to self-report whether or not their partner tested for HIV through any modality after enrollment in the study (either in clinic or with self-testing). By virtue of being self-reported and comparable in both study arms, this will enable us to determine if the intervention resulted in higher reported HIV testing for ther partners of study participants. We believe that when we triangulate all this information, we will be able to make a more accurate determination of whether the intervention is effective in promoting HIV testing.

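### The primary outcome is a different event, measured by a different instrument, in each arm, so the arms can differ significantly when true partner testing is identical

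*Protocol*

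**What the plan says.** - **Primary Outcome Measures** (Study Objectives and Hypotheses) names uptake of HIV testing by women's partners within 3 months, then splits the definition by arm: "a report by female study participants that their partner used a self-test; in the control group, this will be uptake of HTC" at the VCT.
- **Statistical analysis** carries the split into the binary variable for the primary logistic regression: "either with a self-test in the case of the intervention group or at a VCT in the case of the control group".
- **Recording uptake of voluntary HTC (control group)** determines whether control partners tested "based on whether the referral vouchers were presented at HTC sites". The vouchers may be used "at LHC or another facility of their choice within and around Kisumu". Research assistants at the three study facilities are to "collect and record the referral voucher numbers (with a unique participant ID code) presented at the HTC sites".
- **Utilization of confirmatory testing (intervention group)** records intervention-arm vouchers too, but to measure confirmatory testing, not the primary outcome.
- **Limitations** acknowledges the "limitations of having self-reported outcomes in the intervention group and an objective outcome in the control group". It plans to inspect used kits and to check vouchers where a confirmatory test is reported. It will also ask women in both groups to "self-report whether or not their partner tested for HIV through any modality after enrollment in the study". This common item is presented as a further comparison; the primary outcome and analysis stay as above.

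**The concern.** Two things differ between the arms besides the randomised intervention.

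1. **The event.** One arm counts use of a self-test; the other counts testing at a VCT. As worded, an intervention partner who tests only at a clinic is not a success.
2. **The instrument.** One arm relies on the woman's account, the other on a voucher record. A control partner who tests without presenting a voucher that is then recorded has no stated way of being counted.

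This is misclassification of the primary endpoint that depends on the arm. A difference in the measured proportions could come from the definitions alone, and a real difference could be hidden by them. The study hypothesis concerns partner testing by whatever route, and the arm-specific variable does not isolate that.

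**Working it through.** **Inputs from the protocol.** 300 women per arm, control rate 20%, target 30%, power 80% (Sample size justification); 1:1 allocation (Randomization). The two-sided 5% level is worded for all *other* tests; I assume it for the primary test as well.

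**Inputs assumed, because the protocol gives none.** T = true proportion of partners testing, identical in both arms; s = share of control tests captured by a recorded voucher; f = share of intervention non-testers reported as having used a kit; c = share of intervention testers who test only at a clinic.

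**Formulas.** Two-proportion z-test with pooled variance, n = 300 per arm, d = pI − pC, p̄ = (pI + pC)/2:

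- se0 = √[2p̄(1 − p̄)/n]; se1 = √{[pI(1 − pI) + pC(1 − pC)]/n}
- P(significant, favouring intervention) = Φ[(d − 1.96 se0)/se1]; for control, replace d by −d.

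**Step 1: the plan's own figure.** For 20% v 30%: se0 = 0.0354, se1 = 0.0351, Φ(0.874) = 80.9%. The required size is 294 per arm without continuity correction. The stated 80% at 300 per arm reproduces, so the sample-size arithmetic is not the problem.

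**Step 2: identical true testing, errors favouring the intervention.** Observed pC = T·s and pI = T + f(1 − T).

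Worked case, T = 30%, s = 80%, f = 0: pC = 0.30 × 0.80 = 0.24, pI = 0.30, d = 0.06, se0 = 0.0363, se1 = 0.0362, Φ(−0.305) = 38%.

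Adding f = 5%: pI = 0.30 + 0.05 × 0.70 = 0.335, d = 0.095, se0 = 0.0370, se1 = 0.0368, Φ(0.614) = 73%.

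| T | s | f | Observed control v intervention | P(significant, favouring intervention) |
|---|---|---|---|---|
| 20% or 30% | 100% | 0 | equal | 2.5% (nominal) |
| 20% | 90% | 0 | 18.0% v 20.0% | 9% |
| 20% | 80% | 0 | 16.0% v 20.0% | 25% |
| 20% | 100% | 5% | 20.0% v 24.0% | 22% |
| 20% | 80% | 5% | 16.0% v 24.0% | 69% |
| 30% | 90% | 0 | 27.0% v 30.0% | 13% |
| 30% | 80% | 0 | 24.0% v 30.0% | 38% |
| 30% | 90% | 5% | 27.0% v 33.5% | 41% |
| 30% | 80% | 5% | 24.0% v 33.5% | 73% |
| 30% | 70% | 5% | 21.0% v 33.5% | 93% |

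If one third of control tests are missed at T = 30%, the observed rates are 20% v 30%, which is the whole design effect, with an 81% chance of significance. Simulation of 200,000 trials agreed with the formula in the cases checked.

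**Step 3: identical true testing, error favouring control.** With s = 100% and f = 0, observed pI = T(1 − c). For c = 25%:

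- T = 30%: 30.0% v 22.5%; significant in favour of control in 55% of trials.
- T = 20%: 20.0% v 15.0%; 36%.

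The errors can also offset. With T = 30%, s = 80% and c = 25%, the observed rates are 24.0% v 22.5% (0.30 × 0.80 v 0.30 × 0.75).

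**Step 4: power if the common any-modality item is primary.** It would count every control test, so the control rate may exceed 20%. With 300 per arm:

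| Control rate | Power for +10 points | Detectable difference at 80% power |
|---|---|---|
| 20% | 81% | 9.9 points |
| 30% | 73% | 10.9 points |
| 40% | 69% | 11.4 points |

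**The case against.** The strongest reply is that the protocol has seen this problem. Limitations names the asymmetry, plans inspection of used kits and voucher checks, and collects a like-for-like self-report in both arms expressly to reduce bias. What remains is which of two planned measures is called primary. That is a fair description of the residual defect. It still matters, because the primary regression uses the arm-specific variable, and triangulation comes with no rule for what prevails if the measures disagree.

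Several stronger readings are tempting but not supported:

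- **That the bias can only favour the intervention.** Missed control tests and over-reported kit use do favour it, but leaving out clinic-only tests by intervention partners works the other way (Step 3). The net direction is unknown.
- **That vouchers are recorded at three facilities and nowhere else.** The protocol places research assistants at three sites but does not say that tests elsewhere go unrecorded. Control Group encourages use of a study facility and offers a token, which should limit leakage.
- **That the intervention reports go unchecked.** Counselors will ask to see used kits. The checked measure is simply not the primary one.
- **That a control woman lost to follow-up counts as not tested.** No missing-data rule is stated, and such a rule may sit in an analysis plan not at hand.
- **That discussion of testing is also defined differently by arm.** The secondary outcome list and the follow-up data list give one common item. The arm-specific questions under Follow-up interviews do not exclude it.

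There is also some looseness about the control source: Statistical analysis speaks of the partner being reported to have tested, which could be read as self-report. The control-group recording section and Limitations point to the voucher record.

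Finally, self-report in both arms is no cure-all. Women know their allocation, and those handed kits may over-report. At 20% true testing, 5% over-reporting by intervention non-testers gives 22% false significance even with perfect control capture. This stands, and is why a verified-outcome sensitivity analysis is needed.

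**Conclusion.** The point holds. As written, the primary outcome compares reported self-test use with voucher-recorded clinic testing, and a significant difference would not by itself show a difference in partner testing. With 30% true testing in both arms, the chance of a false result favouring the intervention rises from 2.5% to 38% at 80% control capture, and to 73% with 5% over-reporting as well. The chance of one favouring control reaches 55% if a quarter of intervention testers use only a clinic. These sizes rest on assumed capture, over-report and clinic-only rates; they show how sensitive the comparison is and do not predict the trial's bias. The mismatch in event and instrument rests on the protocol's wording alone. Disclosing it under Limitations does not change the primary analysis.

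**What to change.** 1. In Primary Outcome Measures and Statistical analysis, make the common item primary: *partner tested for HIV by any method since enrolment*, asked with the same wording at the same 3-month interview in both arms.
2. Keep the present arm-specific measure as a secondary outcome.
3. Add a sensitivity analysis on verified outcomes: inspected used kit or recorded voucher in the intervention arm, against recorded voucher in the control arm.
4. Restate Sample size justification for control rates above 20%, using the figures in Step 4.

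**Cost.** The item is already to be collected, so the change is to wording and the power statement. The drawbacks should be stated openly. The primary outcome becomes self-reported in both arms and can still be reported differently by unblinded women. If the control rate is 30% or 40%, 300 per arm gives 73% or 69% power for the 10-point target, so the sponsor must either accept a larger detectable difference or revisit the sample size.
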